### Target PCP practices

The intervention will be conducted at four MGH primary care practices; each PCP practice consists of multiple sub-practices called pods.

### Recruitment strategy

All patients in participating primary care clinics will be offered screening for the symptoms of depression by the Patient Health Questionnaire-2 (PHQ-2) as part of their routine primary care visit [23]; data on age, gender, race, ethnicity and primary language will be obtained at the time of screening. Asian American and Latino American patients who screen positive for clinical depression will be called by study staff and invited to participate in the CFP consultation intervention. Patients also may be referred by participating PCPs. For the qualitative interviews, a subset of study participants will be invited to participate after the six-month follow-up visit, as well as eligible members of the target population who not participate in the study.

### Randomization scheme

Primary care patients at MGH will be randomized by pods, which comprise multiple clusters of 5-6 PCPs within each practice site. Using electronic medical records data from 2007, practices will be matched based on an index composed of two variables: 1) the number of patients who are members of the target minority groups and 2) the rate of diagnosed depression. Within each pair, one practice will be randomized to participate in the intervention and the other will be assigned to the "usual care" arm.

### Target Health Condition

All patients in the intervention and usual care (control) arms will be screened for clinical depression using the self-rated PHQ-2 at their primary care visit. Both patients and PCPs will be notified of positive screening results for all patients assessed. For the intervention arm, diagnoses of specific depressive disorders (major depressive disorder, dysthymia, depressive disorder NOS, adjustment disorder with depressed mood) will be established during the baseline clinical interview using DSM-IV-TR criteria [21].

### Definition of Usual Care

PCPs of those patients who screen positive on the PHQ-2 in the usual care arm will receive written feedback on their patients' PHQ-2 results, in addition to a standard list of referrals to MGH mental health resources. At the end of the study, patients in the usual care arm will be offered the intervention.

### Human Subjects Approval

All study procedures have been approved by the hospital Institutional Review Board (IRB).

### Analytic Plan

*Description of Measures *(See Table 1):

**Table 1 T1:** Patient measures administered over study period.

PATIENT MEASURES BY TIMEPOINT					
	**Screen**	**Baseline Assessment**	**2 Week Follow-Up^+^**	**6 Month Follow-Up^+^**	**Qualitative Interview^+^**

MINI International Neuropsychiatric Interview (MINI)*		X			

Quick Inventory of Depressive Symptomatology (QIDS-SR)		X		X	

Resource Utilization Questionnaire		X		X	

CFP Consultation, Assessment & Toolkit*		X	X		

Global Assessment of Functioning (GAF)*		X			

Patient Health Questionnaire (PHQ-2)	X				

Patient Satisfaction Questionnaire				X	

Schwartz Outcome Scale (SOS-10)		X	X	X	

Demographic Questionnaire		X			

Qualitative interview					X

*Intervention arm only.

^+ ^Visit may be conducted by phone.

### Initial Screen

On the screening form, patients will be administered the PHQ-2 and asked additional questions about gender, age, race, ethnicity, and language spoken at home. Using a cutoff score of two or above (out of a possible total score of six), the PHQ-2 has been validated for diagnosing any clinical depressive disorder with a 82.1 percent sensitivity, 80.4 percent specificity, and a positive predictive value of 48.3 percent (assuming 18 percent prevalence of any depressive disorder) [23]; it consists of the first two questions of the PHQ-9, which has been translated into Chinese, Vietnamese, and Spanish [23-27]. The screening form will be available in multiple languages (English, Spanish, Chinese, and Vietnamese).

### Baseline Visit

Both patients in the intervention and usual care arm will give consent to participate in the study at the beginning of the baseline visit. In the intervention arm, assessment measures used at baseline to characterize the intervention patient population will include the Mini International Neuropsychiatric Interview (MINI) [28], Quick Inventory of Depressive Symptomatology-Self Rated Scale (QIDS-SR) (see Appendix 2) [29], Global Assessment of Functioning (GAF) [21], and Schwartz Outcome Scale (SOS-10) [30]. Questionnaires regarding the patients' demographics and utilization of resources will also be assessed. In the usual care arm, for target minorities who screen positive, the assessment measure will include the QIDS-SR and SOS-10.

### Six-month follow-up

Patients will have the option to complete the visit over the phone or in person. In both the intervention and usual care arms, patients will be given the QIDS-SR self-rated questionnaire and asked a brief "Resource Utilization Questionnaire" with questions regarding use of antidepressant medications, referrals/visits to mental health specialists, or alternative providers both in and out of the MGH system. The electronic medical record will also be reviewed at baseline and at the six-month follow-up for both intervention and usual care arms to obtain depression diagnoses, prescription of antidepressant medications, and referrals/visits to mental health specialists in the system.

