Mischoulon et al. reported that screening in primary care settings may not be enough; independent screening by psychiatrists in primary care settings may not be adequate to ensure appropriate management of depression by PCPs [16]. In this study, patients were screened for MDD in a community-based primary care health center. For those who met criteria for MDD, a letter was mailed to their PCP informing them of their patient's diagnosis of MDD. Forty outpatients, of whom 29 (72 percent) were Latino American, were found to meet criteria for MDD. Medical record charts were reviewed 3 months later to determine the PCPs' management following the diagnosis. Of the 38 patients who remained in the study at 3 months, 20 (53 percent) received no intervention for depression from the PCP, and of these, 14 (70 percent) were Latino American. Only five (13 percent) were prescribed an antidepressant by their PCP, nine (24 percent) were referred to mental health services for medication, psychotherapy or combination treatment, and four (11 percent) were prescribed an antidepressant and then referred to mental health services. Mischoulon and colleagues concluded that possible explanations for this lack of treatment of depression may include time constraints during primary care visits, patient and/or physician reticence, and insufficient education of PCPs about clinical depression. These findings suggest that screening and notification must be supplemented by additional interventions if they are to have an impact on the care of depression.

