## Methods/Design

### Overview

This is a randomized controlled trial of the CFP intervention. During the study period, all patients in participating primary care clinics will receive a screening form for symptoms of depression; data on age, gender, race, ethnicity and primary language will be obtained at the time of screening. Asian American and Latino American patients who screen positive for clinical depression will be contacted by study staff and invited to participate in the CFP study. Eligible patients will be randomized either to the intervention arm or usual care based on their primary care provider. Patients in the intervention arm will receive the CFP intervention over two visits and then called at six-months by study staff to administer follow-up questionnaires (described below). Patients in the usual care arm will be called at baseline and at six-month follow-up by study staff to administer questionnaires (described below). To evaluate the cultural components of the study, a number of qualitative interviews will also be conducted with participants in the intervention and usual care arms, and with members of the target population who did not participate in the study. Please see Figure 1 for the study flowchart.

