### Exploratory analysis

Descriptive analyses will be performed to provide information related to the study's experience conducting the initial screening patients within their primary care clinics.

Data from initial screens will be utilized to provide a greater description of the patient population at screening, recruitment and enrollment (e.g., race; ethnicity; preferred language; age; gender; level of depression (i.e., PHQ-2 score); service utilization, as well as identify which of these variables, if any, served to influence participation in the study. This information will allow us to describe, for example, whether consent to be contacted differs by level of depression and whether this is moderated by demographic factors (e.g., race, ethnicity, gender). Additionally we will provide additional data describing rates of enrollment as compared to the total screened.

Secondary exploratory analyses will explore the impact of the intervention on depression. Patients' scores on the QIDS-SR will be compared between the usual care and intervention arms. To measure changes in racial and ethnic disparities in depression recognition and treatment, rates of depression diagnoses will be compared from baseline to six-month follow-up for the intervention and usual care arms. As measures of the use of any ongoing specialty mental health care, the rates of prescription of pharmacotherapy and referrals/visits to mental health specialists as provided by patient self-report will be compared at baseline and at the six-month follow-up. Data analysis will be conducted using STATA statistical software [35].

A general linear model that accounts for clustering at the PCP level will be used. Analyses of the main outcomes will include as covariates any patient or physician factors that differed significantly between study arms. Outcomes regarding diagnosis and treatment will be assessed using general estimating equations with a binomial link and standard errors will be adjusted to account for clustering within practice. Separate analyses will be conducted for each outcome (i.e., dependent variables) -- changes in depressive symptoms, diagnosis of and treatment (prescription of antidepressant medications; referrals/visits to mental health specialists) for depression at six months after enrollment. The effect of study arm on each outcome will be assessed, controlling for significant differences emerging from the bivariate analyses.

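### The chart baseline falls after patient and PCP are told of the positive screen, so responses to that notice can count as baseline status and may distort the exploratory change-from-baseline comparisons

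*Protocol article*

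**What the plan says.** All references are to the Protocol article. The order of events has to be put together from several sections.

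- **Screening.** Under Target Health Condition, patients in both arms "will be screened for clinical depression using the self-rated PHQ-2 at their primary care visit".
- **Notification.** The same section says: "Both patients and PCPs will be notified of positive screening results for all patients assessed". The notice therefore does not depend on enrollment. Definition of Usual Care adds that usual-care PCPs "will receive written feedback on their patients' PHQ-2 results, in addition to a standard list of referrals to MGH mental health resources". No such list is described for intervention PCPs.
- **Recruitment.** Under Recruitment strategy, "Asian American and Latino American patients who screen positive for clinical depression will be called by study staff and invited to participate". No interval is stated.
- **Baseline.** Baseline Visit places consent, in both arms, at the start of that visit. The Overview says: "Patients in the usual care arm will be called at baseline and at six-month follow-up by study staff". In the intervention arm, baseline includes a clinical interview at which depressive diagnoses are made (Target Health Condition).
- **Chart review.** Six-month follow-up states: "The electronic medical record will also be reviewed at baseline and at the six-month follow-up for both intervention and usual care arms". It collects depression diagnoses, antidepressant prescriptions, and mental health referrals and visits.
- **Analysis.** Exploratory analysis compares diagnosis rates between baseline and six months by arm, and compares self-reported treatment and referral rates at the same two times. It also models the effect of arm on diagnosis and treatment "for depression at six months after enrollment", with covariates for patient or physician factors that differ significantly between arms.

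**The concern.** These comparisons are meant to show whether recognition and treatment of depression change. The trial's own prompt to recognise depression, the notice to patient and PCP, is issued before the point from which change is measured. Allocation is already settled by then: it follows the PCP's practice or pod, and the usual-care notice is itself arm-specific. What a PCP does between notice and baseline is thus a post-allocation response, yet it can enter the analysis as a starting value.

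This matters in two ways. First, if the early response differs between arms, the contrast in change from baseline moves even when the consultation has no effect. Second, if a treatment imbalance created in this way is significant at baseline, the covariate rule would bring it into the model, which would then adjust for a consequence of allocation.

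Two routes to a difference are visible. Baseline is a telephone call in usual care and a clinician interview in the intervention arm, so the delays may differ. The notice may also differ in content, since the referral list is described for one arm only.

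**Working it through.** **Sequence.** Set side by side, the sections give: PHQ-2 at the primary care visit, notice to patient and PCP, recruitment call, then consent and baseline with chart review, then the endpoint six months after enrollment. No date of notification is stated; its place before baseline is read from this order. In the intervention arm, recommendations reach the PCP only after the two-week visit (Description of Intervention), so the consultation's own message comes wholly after baseline.

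**Plan's own figure.** There is none to reproduce: the document gives no delay and no expected response to the notice.

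**Input from the document.** Preliminary Studies reports a study in which PCPs were told by letter that a patient met criteria for MDD. Of 38 patients at 3 months, "20 (53 percent) received no intervention for depression from the PCP". The remainder is 5 + 9 + 4 = 18, and 18/38 = 47.4%.

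**Assumptions, for illustration only.** The same response applies here and is identical in both arms. F(w) is the share acted on w weeks after notification, with 3 months taken as 13 weeks. Two shapes are used:

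- linear: F(w) = 0.474 × w/13, flat after week 13;
- constant hazard: F(w) = 1 − exp(−λw), with λ = −ln(20/38)/13 = 0.0494 per week (0.214 per month).

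**Share acted on before baseline.**

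| Delay | Linear | Constant hazard |
|---|---|---|
| 2 weeks | 7.3% | 9.4% |
| 4 weeks | 14.6% | 17.9% |
| 6 weeks | 21.9% | 25.6% |

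**Shift in the contrast (intervention minus usual care) in change from baseline, with no intervention effect.** Taking six-month cumulative status as equal, the shift is −[F(intervention delay) − F(usual-care delay)].

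- Usual care 2 weeks, intervention 6 weeks: −(21.9 − 7.3) = −14.6 points (linear); −(25.6 − 9.4) = −16.2 points (constant hazard).
- Usual care 4 weeks, intervention 2 weeks: −(7.3 − 14.6) = +7.3 points; −(9.4 − 17.9) = +8.5 points.
- Equal delays: 0.

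These are not bounds. With usual care at 1 week and intervention at 8 weeks, the same formula gives −25.5 and −27.8 points.

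**Moving the far end.** Six months runs from enrollment, so a longer delay also means longer since notification. Under the linear shape this changes nothing, because F is flat by then. If the constant hazard is extrapolated to 26 weeks after baseline, the change is exp(−λ × delay) × [1 − exp(−26λ)], where the bracket is 0.723:

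- delays of 2 and 6 weeks: 65.5% v 53.8%, a shift of −11.7 points;
- delays of 4 and 2 weeks: 59.3% v 65.5%, a shift of +6.2 points.

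**Status at six months.** With delays of 1 month (usual care) and 2 months (intervention), the extrapolated cumulative rate is 1 − exp(−0.214 × 7) = 77.6% v 1 − exp(−0.214 × 8) = 81.9%, about 4 points. The change from baseline for the same delays is 58.4% v 47.1%, about 11 points. The endpoint comparison is therefore less exposed, and the distortion has the opposite sign.

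**The case against.** A reader might infer that the comparison is biased, that the intervention arm must be the slower one, and that the bias runs about 11 points against it. The document does not support that.

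- No delay is given for either arm, so 1 month against 2 is an assumption. The telephone route in usual care is stated in the Overview, but Baseline Visit speaks of a visit in both arms, and Table 1 does not mark baseline among the contacts that may be made by phone.
- The 47% followed a letter stating a diagnosis of MDD. Here the notice reports a PHQ-2 at a cutoff of two, with a quoted positive predictive value of 48.3% (Initial Screen). A weaker signal may prompt less action. The constant hazard past 3 months is extrapolation. If PCPs act mainly at or soon after the screening visit, early response would be similar in both arms whatever the delay.
- The article also analyses the arm effect at six months after enrollment, which is less exposed.
- Notification goes to both arms, so the question is what the consultation adds to it, and enrollment is a defensible origin for that.
- Index dates and look-back windows are often left to an abstraction manual or SAP. A review made at baseline need not count entries after screening as baseline status.
- Silence about a referral list for intervention PCPs, in a condensed article, does not show that they receive none.

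These points stand, and they remove any claim to a known size or direction. They do not remove the problem of sequence: the article itself fixes baseline as the reference point and places notification before it.

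**Conclusion.** The concern holds in a conditional form. The stated order of events allows post-allocation responses to the screening notice to be counted as baseline status in the exploratory diagnosis and treatment comparisons. If those responses differ by arm before baseline, through delay or through the content of the notice, the change-from-baseline contrast is distorted, and adjusting for a resulting treatment imbalance would adjust for a post-allocation response.

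The illustrative shifts of roughly -16 to +9 points show only that the effect could be material. They rest on assumed lags, on a response rate borrowed from patients with MDD, and on six-month cumulative status being equal in the two arms. Equal delays with equal response give no shift.

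The primary aim (feasibility, satisfaction and cost) does not rest on these contrasts. They still merit care, because Sample size and power says that the exploratory results will inform further iterations of the intervention and design.

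**What to change.** - **Chart baseline.** In both arms, define baseline status (diagnosis, antidepressant, referral) as what was on record before the PHQ-2 screening visit, and count new entries from the screening date onward.
- **Reporting.** Give the screen-to-baseline interval by arm.
- **Endpoint.** Keep six months after enrollment. Add a sensitivity analysis with an equal window from the screening date in both arms. Use chart-recorded prescriptions and referrals for it, because the self-reported baseline cannot be re-dated.
- **QIDS-SR.** Do not adjust this comparison for the interval. If the interval is driven by arm, adjustment could absorb part of the arm effect.

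The cost is small: the chart review and the screening event already exist, so the change is to abstraction dates and analysis wording. There are two drawbacks. The chart baseline will no longer match the questionnaire baseline. In the sensitivity analysis, an intervention arm that reaches baseline more slowly has less time after its consultation, so that result needs to be read beside the enrollment-based one.

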### Sample size and power

Initially, we planned for a total sample size of 506 patients, split evenly between the intervention and usual care groups. We calculated this sample size to yield 84 percent power to detect a difference in the reduction of depressive symptoms on the QIDS-SR by 50 percent in the intervention arm versus 35 percent in the treatment arm, paralleling the experience of patients in the intervention arm in STAR*D, an multi-center effectiveness study of Major Depression in primary care settings [31] as well as the experience of patients in usual care arm in several studies [32-34]. However, given the multiple recruitment challenges we have faced to date, we have revised our total sample size to 120 patients, split evenly between intervention and usual care groups. Although this sample size is significantly smaller, the results of both the qualitative and exploratory analyses of this study will inform further iterations of this intervention and study design.

### Qualitative analysis

The project's implementation process and satisfaction (providers' and patients') with the CFP consultation intervention will be assessed in several ways. Qualitative data will be collected through interviews, meetings and conversations with the project and primary care practice staff, as well as reviews of project records and meeting summaries. Interviews will be transcribed and translated, with content analysis used to assess for convergent and divergent themes.

The patient interviews will include samples of Asian American and Latino American patients. In addition, interviews will be conducted with members of the target population who did not participate in the study. The interviews will be conducted by telephone, or in person as needed. The interviews will assess the extent of patients' involvement with the project or perception of this kind of intervention. All participants will be asked for their opinions about offering this service through their primary care office and the screening process. In addition, intervention participants will be surveyed about satisfaction, use of the toolkit, opinions about the cultural tailoring of the intervention, and asked for their suggested changes to the intervention. Intervention patients will also be asked about their follow-up on recommendations from the consultation and discussions - if any - with their PCP resulting from the intervention. Usual care participants will be asked about their use of mental health services, their understanding of the study when they enrolled, and their views on what they believe would be important to include within toolkits or a culturally focused psychiatric consultation service.

Using open- and closed- ended questions, the project staff and practice staff (including PCPs, practice managers and frontline staff) will be asked about their perceptions of, experiences with, and satisfaction with the project's implementation, including the screening and referral process. The organizational structure and resources of each participating primary care practice will be characterized at the beginning of the project to assist in the understanding and interpretation of implementation differences across the sites. Through the review of organizational data and regularly collected project data and the interviews, the identified organizational issues will be addressed with the practices, possibly identifying the need for procedural changes or additional staff training.

Additionally, the costs of implementing and continuing the program will be assessed. Initial startup costs and the ongoing costs of the intervention will be tracked. Both the direct dollar outlays associated with program implementation and the dollar values of program resources not reflected in the program budget will be calculated. While the project budget and expenses can be calculated directly from project data, work will be done with practices to estimate the cost of consultations and coordinating care.

Other questions to be asked within this cost analysis will be whether patients' utilization of practice and hospital services--including primary care, emergency department and inpatient visits and their associated costs--changed as a result of participating in this project. Costs of the care provided to the patients will also be compared to the cost of usual care in the control group. Using the figures above, the total range and average costs of care for the patients receiving the intervention will be calculated. A preliminary analysis also will be undertaken to look at differences in the use of services in the treatment versus the control group, i.e., if the two groups differ in their utilization and costs of primary care, emergency department visits and inpatient care. Such cost analyses may provide preliminary estimates of the costs of implementing such interventions in academic medical centers.

